### Outcome measures and endpoints

2.6

The Korean version of the FMA motor score will be used to measure the primary endpoint.^[19]^ The motor domain of FMA ranges from a score of 0 (flaccid hemiplegia) to 100 (normal movement), with 66 points for the upper limb and 34 points for the lower limb. An educated physiotherapist will perform all motor assessments at baseline and weeks 4, 8, and 12. The K-NIHSS and Korean versions of the modified Rankin scale (K-mRS), the modified Barthel index (K-mBI), and the montreal cognitive assessment (MoCA-K) will be used at baseline and weeks 4 and 12.

The primary efficacy endpoint is the change in FMA motor score at week 12 from the baseline. The secondary efficacy endpoints are: the change in FMA motor score at weeks 4 and 8 from the baseline; the change in FMA motor score at weeks 4, 8, and 12 from baseline according to the timing of treatment initiation after the onset of stroke (either within 1 week or 1–2 weeks) or according to the presence of prognostic risk factors (hypertension, diabetes, dyslipidemia, etc); the change in K-NIHSS and K-mRS scores at weeks 4 and 12 from the baseline; the proportion of subjects with a K-NIHSS score of 0 to 2 at week 12; the proportion of subjects with a K-mRS score of 0, ≤1, and ≤2 at week 12; and the change in K-MBI score at weeks 4 and 12 from the baseline. Exploratory endpoint is the change in MoCA-K score at week 12 from baseline.

Safety endpoints are the adverse events, significant changes in vital signs and physical examination; and abnormal laboratory tests, electrocardiogram, and chest radiography results. Laboratory tests will include hematology, electrolyte, blood chemistry, lipid battery, blood coagulation, and urinalysis.

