### Sample size

2.7

The primary endpoint of the study is the change in FMA motor score at baseline from that after 12 weeks. A sample size of 22 in each group will be sufficient to detect a clinically important difference of 14.5 points on the FMA score, assuming a standard deviation (SD) of 19.2. This estimate is based on the findings of the fluoxetine in motor recovery of patients with acute ischemic stroke trial, which reported a difference of mean ± SD 90-day FMA score change between fluoxetine group (n = 57, 36.4 ± 21.3) and control group (n = 56, 21.9 ± 16.7).^[20]^

Because this HT047 trial is a phase 2 exploratory clinical trial for appropriate dose selection, we did not consider adjustment to control for type 1 errors resulting from the comparison between the 3 groups. However, in the comparison of primary efficacy outcome between the 3 groups, multiple comparisons will be performed to control for the experiment-wise error rate. We will use a Student *t* test of the difference between mean values, a power of 80%, and a significance level of 10%. With a 15% anticipated drop-out rate considered, we plan to enroll 26 patients per group (a total of 78 patients).

The formula for the sample size for comparison of 2 mean values is as follows:
 
[figure not shown]

where *Z*_*α*/2_ is the normal distribution threshold of type 1 error (*α* = 0.10/2), *Z*_1-*β*_ is the normal distribution threshold of power (1 − β = 0.8), *μ*_*T*_ is the mean change of 12-week FMA score in HT047 group (high dose or low dose), *μ*_*C*_ is the mean change of 12-week FMA motor score in control group, and σ is the standard deviation.

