### Statistical analysis

2.8

Efficacy will be assessed in the full analysis set (FAS) and the per-protocol (PP) set. The FAS will include all subjects who meet the inclusion/exclusion criteria, provide voluntary informed consent to participate in the study, receive at least 1 dose of the investigational product after randomization, have FMA assessment, that is, the primary efficacy endpoint, at screening, and at least once at weeks 4, 8, or 12 during the follow-up period. The PP set will include all FAS subjects who do not have any major violations such as major protocol violations (excluding minor violations) and have a primary efficacy assessment per protocol. Subjects with an overall medication compliance of <70% will be excluded from the PP set. Safety will be assessed in the safety set, which will comprise of all subjects who receive at least 1 dose of the investigational product after randomization.

The primary efficacy endpoint will be analyzed both in the FAS and the PP sets. The final conclusions of the study will be made based on the FAS results, in principle. Mean, SD, median, and range (minimum, maximum) of FMA motor score before dosing and 12 weeks after dosing, as well as score change between the 2 time points, will be presented for the high- and low-dose HT047, and the placebo groups. To assess intergroup differences in the primary endpoint, that is, FMA change, analysis of covariance, with baseline FMA as a covariate, and Tukey multiple comparison test will be carried out. Dunnett multiple comparison, which would consider the placebo group as a comparator group, will not be used because this phase 2 study aims to evaluate adequate dosage and therefore, will compare the HT047 high-dose group with the HT047 low-dose group.

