A comprehensive statistical analysis plan will be finalized prior to database locking. Details of statistical analyses that are not presented in the protocol will be described in the statistical analysis plan. All statistical analyses will be performed at a 2-sided significance level of 10%. To handle the missing data, the last observation carried forward method will be used for FMA motor score, the primary outcome variable. If FMA motor score is measured only at screening, substitution for missing data will not be performed. Similarly, for the other outcome variables, missing data will not be substituted and included in the statistical analysis. Interim analysis will not be performed.

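### Carrying the last FMA score forward to week 12 treats recovery as halted at drop-out: a modest attenuation at the planned 15% drop-out, larger if drop-out differs by arm

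*Protocol article*

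**What the plan says.** All of this is in the protocol article.

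- Outcome measures and endpoints: "The primary efficacy endpoint is the change in FMA motor score at week 12 from the baseline". On timing, "An educated physiotherapist will perform all motor assessments at baseline and weeks 4, 8, and 12".
- Statistical analysis, model: "analysis of covariance, with baseline FMA as a covariate, and Tukey multiple comparison test will be carried out".
- Statistical analysis, missing data: "the last observation carried forward method will be used for FMA motor score, the primary outcome variable". The one limit is "If FMA motor score is measured only at screening, substitution for missing data will not be performed", so only a week-4 or week-8 score can be carried to week 12.
- Statistical analysis, analysis set: a patient enters the full analysis set (FAS) with an FMA "at least once at weeks 4, 8, or 12 during the follow-up period", and "The final conclusions of the study will be made based on the FAS results, in principle".
- Sample size: the effect and SD come from a fluoxetine trial with 90-day FMA gains of 36.4 (SD 21.3) and 21.9 (SD 16.7). Enrolment is set "With a 15% anticipated drop-out rate considered" at 26 per group.

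The article gives no reason for carrying scores forward and names no missing-data sensitivity analysis for the primary endpoint. The per-protocol analysis is a second population, not a second way of handling missing scores. Generalized estimating equations are planned for secondary FMA endpoints, but week 12 appears there only in the subgroup comparisons.

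**The concern.** Treatment starts within 2 weeks of the stroke, and the planning figures imply that FMA rises substantially over the following three months in every arm, placebo included. Carrying a week-4 or week-8 score to week 12 assumes that recovery stops on the day the patient leaves. The primary estimate then mixes 4-, 8- and 12-week changes, although the endpoint is defined at week 12.

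Two things follow. If the drug works, the contrast is attenuated even when drop-out is equal, because the active arm has more recovery left to lose. If drop-out differs by arm, the contrast can move even when the drug does nothing. The same applies to the high-dose versus low-dose comparison, which the article gives as its reason for choosing Tukey over Dunnett. The method is fixed in the article, so it is not a detail left to a later analysis plan.

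**Working it through.** **1. The plan's own figure.** Pooled SD = √[(56 × 21.3² + 55 × 16.7²)/111] = 19.16, matching the stated 19.2. The difference is 36.4 − 21.9 = 14.5. With two-sided α = 0.10 and 80% power, n = 2 × [19.2 × (1.645 + 0.842)/14.5]² = 21.7, so 22 per group. Then 22/0.85 = 25.9, so 26 per group and 78 in total. The stated sample size reproduces.

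**2. Formula for the shift.** Inputs from the article: muT = 36.4, muC = 21.9, drop-out 15%. Assumed, because the article does not give them: f, the share of the week-12 gain reached at the last visit (same in both arms); the share d of each arm that is carried forward; and drop-out unrelated to the individual's recovery. A carried-forward patient contributes f × mu on average instead of mu, so the arm mean is mu × [1 − d(1 − f)] and the contrast shifts by

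shift = −(1 − f) × (dT × muT − dC × muC).

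**3. Planned drop-out, equal in both arms (15%).** The shift is −(1 − f) × 0.15 × 14.5.

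- f = 0.4: −1.3 points
- f = 0.5: −1.1 (contrast 13.4)
- f = 0.7: −0.7 (contrast 13.8)
- f = 0.9: −0.2

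With 26 per arm and SD 19.2, normal-approximation power is 86% with complete data. It is about 81% at f = 0.5 and 83% at f = 0.7, and stays between about 80% and 85% over the whole range of f.

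**4. Unequal drop-out (hypothetical).** Take 55% of the gain at week 4 and 82% at week 8, with drop-out split evenly between the two later intervals. Then f averages (0.55 + 0.82)/2 = 0.685 and 1 − f = 0.315.

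| Active / placebo | dT × muT − dC × muC | Shift | Contrast if truth is 14.5 |
|---|---|---|---|
| 15% / 15% | 5.460 − 3.285 = 2.175 | −0.69 | 13.8 |
| 20% / 10% | 7.280 − 2.190 = 5.090 | −1.60 | 12.9 |
| 25% / 5% | 9.100 − 1.095 = 8.005 | −2.52 | 12.0 |
| 12% / 18% | 4.368 − 3.942 = 0.426 | −0.13 | 14.4 |
| 5% / 25% | 1.820 − 5.475 = −3.655 | +1.15 | 15.7 |

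**5. No drug effect.** With both arms at 21.9, the false difference is 0.315 × gap × 21.9: 0.69 points for a 10-point gap and 1.38 for a 20-point gap, favouring the arm with less drop-out. With equal drop-out it is zero. For a 20-point gap, the two-sided error rate rises from 10% to about 11.0% at f = 0.7 and 12.9% at f = 0.5.

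**6. When the direction turns.** The shift is zero when f = 1 (recovery has plateaued) or when dT × muT = dC × muC. With the planning means, the second case is dC/dT = 36.4/21.9 = 1.66.

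**7. Simulation check.** Settings: two arms of 26, week-12 SD 19.2, visit SDs 0.75, 0.90 and 1.00 of that, adjacent-visit correlation 0.85, f as in step 4, and drop-out either random or dependent on the last observed change. Carrying forward gave 13.8 to 14.0, 12.9 and 12.0 for the first three rows of the table. A sequential-regression estimator that is valid under missing at random gave 14.5 to 14.6. Standard errors were about 5.2 to 5.5 and 5.5 to 5.6 respectively.

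**The case against.** The strongest reply is that, in the only drop-out scenario the article supports, the harm is small and conservative. It gives 15% overall and predicts no difference between arms. A loss of about 0.7 points against a standard error of about 5.3 is roughly 0.13 of a standard error. In root-mean-square terms, √(5.3² + 0.7²) ≈ 5.35, no worse than an unbiased estimator with a standard error of 5.5. At 20% versus 10% the two are about level. Carrying forward clearly loses only at gaps such as 25% versus 5%. This stands, and it limits the weight of the point.

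Exposure may also be lower than assumed. Patients lost before week 4 leave the FAS and are not imputed, so 15% carried forward is an upper figure for that scenario. A repeated-measures model restricted to observed post-baseline scores would not recover those patients either.

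The comparison in step 7 favours the alternative partly by construction, because missing at random held in every simulated scenario. Drop-out driven by unobserved decline was not tested, and the estimator was sequential regression, not the mixed model proposed below.

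Three stronger readings are tempting, and the documents do not support them:

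- A reader might infer that the contrast is biased whenever drop-out differs or the drug works. Step 6 shows that the bias vanishes at a plateau or by cancellation.
- A reader might infer that more drop-out on placebo always favours HT047. That holds with no drug effect. With an effect of the planned size, placebo drop-out must exceed about 1.66 times active drop-out; at 12% versus 18% the shift is still against HT047.
- A reader might infer that heavier drop-out on HT047 is to be expected in a first-in-human study. The article gives no figure for this.

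**Conclusion.** The point holds as a cheap improvement that should be made, not as a flaw that invalidates the trial. The primary analysis fixes an assumption, no recovery after drop-out, that conflicts with the article's own planning figures, and it does so in the analysis set that decides the conclusion. At the planned, equal 15% drop-out, the cost is an attenuation of about 0.2 to 1.3 of 14.5 points, and less if some patients are lost before week 4. The method gives no protection if drop-out turns out to differ by arm: then the shift is about 1.6 to 2.5 points in the two cases with more drop-out on active drug, with a false difference of about 0.7 to 1.4 points if the drug does nothing.

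These sizes rest on assumed recovery shares, a common share in both arms, and drop-out splits that the article does not give. For any given drop-out split, the direction of the shift is the same for every f below 1.

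**What to change.** Make the primary analysis a mixed model for repeated measures of FMA change at weeks 4, 8 and 12. Include treatment, visit, treatment-by-visit and baseline FMA by visit, with unstructured covariance and Kenward-Roger degrees of freedom. Take the Tukey-adjusted week-12 contrasts as primary, which keeps the planned high-dose versus low-dose comparison. Keep the analysis of covariance on carried-forward scores as a sensitivity analysis.

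No new data or visits are needed. The cost is a change of wording in the protocol and analysis plan before database lock, a slightly larger standard error (about 5.5 against 5.3 in the simulation), and reliance on missing at random, which should be stated. Whether to add hospital as a covariate is a separate question and not part of this change.

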### Data management and monitoring

2.9

All data will be entered and stored in a secure electronic data capture system. Site investigators will have direct access to the data set from their own sites and the sponsor will have access to the final trial data set. The identity of subjects will be concealed using a subject identification code in all study documents. Personal information obtained from this trial will be stored for up to 3 years after completion of the trial and will not be provided to anyone not involved in the study. Participating centers will be monitored by on-site visits of trained monitors in accordance with standard operating procedures during the entire course of the study. Source data verification will be performed during monitoring to improve the data quality. A Data Monitoring Committee will not be needed because this is a low-risk study and no interim analysis will occur.

### Harms

2.10

All adverse events will be monitored and recorded, irrespective of causality. The investigators will evaluate the severity of symptoms and the causal relationship to the investigational products. All serious adverse events will be reported to the Institutional Review Board and sponsor within 24 hours. Participants will be compensated for medical expenses related to treatment of injury that is confirmed to be caused by the investigational products or procedure.

### Ethics and dissemination

2.11

This protocol (ver 5.0, issue date July 12, 2017) has been approved by the ethics committees of Kyung Hee University Hospital (KHUH IRB 2016-03-303-037), Kyung Hee University Hospital at Gangdong (KHNMC 2016-02-016-011), Hanyang University Hospital (HYUH 2016-02-017-020), Hanyang University Guri Hospital (GURI 2016-03-003-020), Hanyang University Myongji Hospital (MJH 2016-01-014-025), Gachon University Gil Medical Center (GAIRB2016-102), Hallym University Dongtan Sacred Heart Hospital (HDT 2017-03-194-001), and Chosun University Hospital (CHOSUN 2017-03-010-002), and registered with ClinicalTrials.gov (NCT02828540, July 11, 2016). Written informed consent will be obtained from all the patients based on local ethics committee recommendations. A model consent form is also available from the corresponding author on reasonable request. This study is being conducted in accordance with the Declaration of Helsinki and the Korean Good Clinical Practice guidelines. The full protocol and participant-level data sets generated and/or analyzed during the present study are not publicly available. The results of this study will be published in a peer-reviewed journal

## Discussion

3

Although neuroprotective agents have been tested for efficacy in several preclinical and clinical settings, none have been investigated in large clinical trials for ischemic stroke.^[21]^ Recent studies have assessed the efficacy of several agents, acting through various mechanisms, in patients who underwent thrombolytic treatment.^[1,22]^ Though oriental herbal medicines have been used to treat ischemic stroke for thousands of years, and even to this day, in Asian countries including Korea, China, and Japan, their efficacy remains unclear due to the poor quality of clinical trials. Consequently, clinical practice guidelines do not recommend any neuroprotective agents and herbal products to treat acute stroke in patients.

Certain herbal products have shown neuroprotective effects in clinical trials and have successfully improved poststroke recovery.^[23,24]^ However, these trials lack a randomized, double-blind, placebo-controlled design, which is important to investigate the efficacy of therapeutic interventions. Therefore, there is an unmet need to determine the efficacy and safety of herbal medicines through well-designed studies. Because the active compounds of *P lobata* and *S baicalensis* have been previously shown to have neuroprotective and neurorestorative effects,^[7–18]^ we designed this study protocol to investigate the efficacy and safety of HT047.

The FMA motor score was the primary endpoint to assess motor function. FMA is a quantitative assessment tool developed by Fugl-Meyer et al in 1975 to measure the functional restoration of stroke patients^[19]^ and consists of 5 domains (motor function, sensory function, balance, joint range of motor, and joint pain) with a total score of 226 points with excellent inter- and intrarater reliability and good validity.^[20,25]^ In the FMA, motor function scale has been mostly used, and we will only use the motor function scale in this trial. The evaluation of motor function involves the evaluation of the upper and lower extremities, and of synergy, with the advantage that both the upper and lower limbs can be evaluated simultaneously without any special equipment. The evaluation takes approximately 30 to 45 minutes. In this clinical trial, a specialist in the administration center has conducted offline training for researchers at individual institutions. In addition, we also use common scales including K-NIHSS, K-mRS, K-MBI, and MoCA-K for the secondary endpoint assessment.

This study protocol is not without limitations. First, this is a phase 2 pilot study comprising a relatively small sample size of patients. However, based on the results of this study, a subsequent phase 3 trial will be planned. Second, since our study will enroll patients whose stroke symptoms occurred within the previous 14 days, most patients will be in the subacute stage after stroke. Third, the study's drug formulation is a tablet that will be prescribed 3 times a day; patients with tube feeding due to dysphagia will be excluded. Another limitation is that evaluation of motor function is focused on the upper limb than the lower limb, and it lacks evaluation of fine movement. Further, FMA can also be prone to the ceiling effect. Nevertheless, there are several strengths of this protocol; it has a multicenter, prospective, and double-blind randomized design. In addition, we will investigate high and low doses of HT047, allowing for a stratified analysis for efficacy and safety. Furthermore, the FMA motor scale can provide detailed information concerning poststroke motor outcomes.

In conclusion, this study is a 1st-in-human trial of HT047 in acute ischemic patients. Our results will provide evidence on the efficacy and the safety of HT047 as a treatment to improve poststroke motor function and the appropriate dosage.
